## **10 STATISTICS**

### **9.1 Description of Statistical Methods**

Both a fully detailed study level statistical analysis plan (SAP) as well as a separate Statistical Analysis Plan for the Marketing Authorisation Application (MAA SAP) will be written and signed off before any interim data analyses are conducted.

The data from this study will be included in prospective pooled analyses of studies for efficacy and safety of ChAdOx1 nCoV-19 to provide greater precision of both efficacy and safety outcomes.

#### **10.1.1 Efficacy Outcomes**

The primary efficacy endpoint is PCR\* positive symptomatic COVID-19.

This is defined as a participant with a PCR+\* swab and at least one of the following symptoms: cough, fever  $\geq 37.8$ , shortness of breath, anosmia, or ageusia.

Where possible, sensitivity analyses will be conducted using common alternative definitions of virologically-confirmed COVID-19 disease, including those in use in other phase 3 protocols (including but not limited to: USA AstraZeneca phase 3 trial, South Africa COV005 trial, WHO solidarity trial, CEPI definition). This will aid in comparisons between various studies and meta-analyses. These alternative definitions will be detailed in the statistical analysis plan as exploratory analyses.

\*or other nucleic acid amplification test

### **9.2 Primary efficacy**

The primary and secondary analyses will be conducted on participants who are seronegative at baseline. A sensitivity analysis will be conducted including all participants regardless of baseline serostatus.

Analysis of the primary endpoint will be computed as follows:

1. **Efficacy of two doses of vaccine** where the booster vaccine was a high-dose ChAdOx1 nCoV-19. Only participants who received two doses will be included (LD/SD or SD/SD) and only cases occurring more than 14 days after the second vaccine will be included.

Secondary analysis

2. **Efficacy of at least one standard-dose** of any ChAdOx1 nCoV-19. Cases occurring more than 21 days after the first vaccination will be included if the first vaccine was a high-dose vaccine. For participants who received a low-dose as their first vaccine, only cases occurring more than 14 days after a standard-dose booster will be included. Participants receiving only low-dose vaccines will be excluded.

3. **Efficacy of two standard-doses of vaccine.** Only participants who received two standard-dose vaccines will be included and only cases occurring more than 14 days after the second vaccine will be included.

Proportions will be compared between ChAdOx1 nCoV-19 and MenACWY groups using a Poisson regression model with robust variance . The model will contain terms including treatment group, and age group at randomization if there is a sufficient sample size within each age category. The logarithm of the period at risk for primary endpoint will be used as an offset variable in the model to adjust for volunteers having different follow up times during which the events occur. Vaccine efficacy (VE) will be calculated as  $(1 - RR) \times 100\%$ , where RR is the relative risk of symptomatic infection (ChAdOx1 nCoV-19: Control) and 95% confidence intervals will be presented.

If the Poisson regression model with robust variance fails to converge, the exact conditional method for stratified poisson regression will be used.

Cumulative incidence of symptomatic infections will be presented using the Kaplan-Meier method.

Secondary efficacy endpoints will be analysed in the same way as the primary efficacy endpoint.

Analyses will be conducted for all adults combined as well as conducting analyses stratified by age cohorts.

All data from participants with PCR-positive swabs will be assessed for inclusion in the efficacy analyses by two blinded assessors who will independently review each case according to pre-specified criteria as detailed in the statistical analysis plan, to classify each for inclusion in the primary and secondary outcomes. A separate CRF will be designed for this purpose.

All PCR-positive results will be assessed for the primary outcome, including those with symptoms swabbed by trial staff, those with positive throat swabs from weekly home-testing, and other potential sources of information such as health-care workers who are tested at their workplace as either a routine test procedure or due to developing symptoms.

PCR+ swabs from outside the trial (for example, a workplace routine swab result in a healthcare worker) will be reviewed by blinded staff and only included as a potential endpoint if the test was conducted in 1) a medical laboratory with ISO 15189 accreditation (provided by UKAS in UK) AND 2) an assay that is either CE marked or that has a derogation authorisation from the MHRA.

\*or other nucleic acid amplification test

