|--|------------------------------------------------------------------------------------------------------------------------------------------------------------------------|--------------------------------------------------------------------------------------------------------------------------------------------------------------------------------------------------------------------------------------------------------------------|
|  |                                                                                                                                                                        | 
b) Intensive care unit (ICU) admissions associated with COVID-19
 
c) Deaths associated with COVID-19
 
d) Seroconversion against non-Spike SARS-CoV-2 antigens
 
e) Severe COVID-19 disease (defined according to clinical severity scales)
 |
|  | To assess humoral immunogenicity of ChAdOx1 nCoV-19                                                                                                                    | 
a) Antibodies against SARS-CoV-2 spike protein (seroconversion rates) at Day 28 post-vaccination.
 
b) Proportion of seroconversion to antibodies against SARS-CoV-2 spike protein at Day 28 post-vaccination.
                                         |
|  | To assess cellular immunity of ChAdOx1 nCoV-19 in older adults (groups 1, 2, 7 and 8 only)                                                                             | a) Interferon-gamma (IFN- $\gamma$ ) enzyme-linked immunospot (ELISpot) responses to SARS-CoV-2 spike protein;                                                                                                                                                     |
|  | To assess the safety and immunogenicity of a booster dose of ChAdOx1 nCoV-19 in older adults aged 56 years or older (two-dose schedules for groups 1, 2, 7 and 8 only) | 
a) occurrence of solicited local reactogenicity signs and symptoms for 7 days following booster vaccination;
 
b) occurrence of solicited systemic reactogenicity signs and symptoms for 7 days following booster vaccination;
                         |

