## 9.5 Subgroup analyses

Subgroup comparisons of efficacy, and safety will be conducted by incorporating vaccine-group by subgroup interaction terms into appropriate regression models. Subgroup comparisons will only be conducted if there are at least 5 cases in all subgroups.

Comparisons will include:

1. Males vs females
2. Age (18 to 55 years vs 56-<70 years vs 70+ years)
3. Seropositive to S-spike or non-spike proteins at baseline vs not seropositive
4. Health care workers and highly-exposed participants versus others
5. Standard dose versus low dose

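### Non-convergence is an unreliable trigger for the exact method: with zero cases in one arm, common software reports convergence and an interval of almost no width

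*Protocol*

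**What the plan says.** Protocol section 9.2 Primary efficacy (in the Statistics chapter) fixes the model: "Proportions will be compared between ChAdOx1 nCoV-19 and MenACWY groups using a Poisson regression model with robust variance". On covariates it says "The model will contain terms including treatment group, and age group at randomization if there is a sufficient sample size within each age category", and on follow-up "The logarithm of the period at risk for primary endpoint will be used as an offset variable in the model". VE is one minus the relative risk, with a 95% confidence interval.

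The exact method has a single trigger: "If the Poisson regression model with robust variance fails to converge, the exact conditional method for stratified poisson regression will be used".

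Two further sentences in the section widen the reach of the rule: "Secondary efficacy endpoints will be analysed in the same way as the primary efficacy endpoint", and "Analyses will be conducted for all adults combined as well as conducting analyses stratified by age cohorts". The secondary efficacy outcomes, listed in the Synopsis and in section 4, include hospital admission, "Intensive care unit (ICU) admissions associated with COVID-19", deaths and severe disease.

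The only minimum case count is in section 9.5 Subgroup analyses: "Subgroup comparisons will only be conducted if there are at least 5 cases in all subgroups". It governs interaction comparisons and is not stated per arm. Five cases in a cohort, all of them in controls, would satisfy it.

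**The concern.** The fallback exists for data too sparse for the regression. The plainest such case is an arm with no events, and there non-convergence is a poor signal. The likelihood keeps improving as the log rate ratio goes to minus infinity, but each gain soon falls below the software's tolerance. The routine stops at a large negative value and reports success. The robust variance does not reveal the problem, because residuals in the empty arm shrink along with the fitted means.

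At stake is how the severe-disease endpoints are reported. An endpoint with two control cases and no vaccine cases carries almost no information, yet it could be reported as complete protection with certainty.

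**Working it through.** The protocol states no figure for this rule, so there is none to reproduce. The check is whether the rule behaves as intended.

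**Inputs from the protocol.** The model, offset, optional age term and trigger are from section 9.2. Allocation is 1:1 in the main efficacy groups (section 5). Groups 9 and 10 have about 500 per arm and group 4 up to 1,775 per arm (section 5.1).

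**Assumptions.** Case counts are 0 v 2, 5, 10 and 30. Arm sizes of 4,000 and 5,000 were used besides 500 and 1,775. Follow-up was either equal or uniform between 0.1 and 0.5 years.

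**Step 1, point estimate.** With no vaccine cases the estimated RR is 0 and log RR is minus infinity. Any printed coefficient only shows where the routine stopped.

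**Step 2, robust variance.** For two arms of size n with equal follow-up, Var(log RR) is the sum over arms of Σ(y - μ)² / (Σμ)².

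- Empty arm: nμ² / (nμ)² = 1/n.
- Other arm with c cases: c(1 - c/n) / c² = 1/c - 1/n.
- Sum: 1/c, so SE = 1/sqrt(c).

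**Step 3, robust interval.** For 0 v 10 with 5,000 per arm, the fit gave b = -22.4 and SE = 0.316. The upper limit for log RR is -22.4 + 1.96 × 0.316 = -21.8. Since exp(-21.8) is below 10⁻⁹, the lower limit for VE is 100% to any reportable precision.

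**Step 4, exact interval.** Given c cases in total, the vaccine count is binomial with p = RR/(1 + RR). With none observed, p_U = 1 - 0.025^(1/c), so RR_U = p_U/(1 - p_U) = 0.025^(-1/c) - 1.

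| Cases, vaccine v control | Robust SE | Robust 95% CI for VE | Exact RR_U | Exact lower limit for VE |
|---|---|---|---|---|
| 0 v 2 | 0.707 | 100% to 100% | 5.32 | -432% |
| 0 v 5 | 0.447 | 100% to 100% | 1.091 | -9.1% |
| 0 v 10 | 0.316 | 100% to 100% | 0.446 | 55.4% |

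**Step 5, does the trigger fire?** R glm and statsmodels GLM, both IRLS, reported convergence in every zero-case run, with and without an age term. The statsmodels runs covered tolerances from 1e-6 to 1e-12. BFGS and L-BFGS also reported convergence, with intervals lying between 99.2% and 100%. The statsmodels Newton routine usually reported non-convergence (five of six zero-case fits in one set of runs) and would then have invoked the exact method. With zero control cases the failure is mirrored: at 5 v 0, statsmodels GLM converged to a VE of about -1.8 × 10¹¹% with an equally spurious interval.

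**Step 6, where the collapse ends.** Robust against exact 95% CI for VE, equal follow-up:

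- 1 v 10: 21.9% to 98.7% against 29.7% to 99.8%.
- 2 v 10: 8.8% to 95.6% against 6.1% to 97.9%.
- 4 v 20: 41.5% to 93.2% against 40.3% to 95.0%.

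From one case upward there is no collapse.

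**Step 7, the primary endpoint.** Section 9.6 gives about 90% power at VE 60% for a lower bound above 20%. The vaccine share of cases is 0.4/1.4 = 0.286 at VE 60% and 0.8/1.8 = 0.444 at VE 20%. The events needed are about [(1.96 × 0.497 + 1.28 × 0.452)/0.159]² ≈ 96, of which about 27 would be in the vaccine arm. That analysis is pooled, and this study's share is not stated. Even with only 20 study cases, the chance of none in the vaccine arm at VE 60% is 0.714²⁰ ≈ 0.001.

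**The case against.** The strongest reply is that the trigger can be read as working. No finite estimate exists at zero cases, so in the mathematical sense the model does not converge. The protocol names no software, and with a Newton routine the fallback usually does fire. This stands as far as it goes: a reader might infer that the exact method would never be reached at zero cases, and the runs do not support that. They do show that the same data and the same sentence give either a lower limit of 100% or one of -9%, according to the optimiser.

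A second reply is that such detail belongs in the SAP, which is not at hand and may contain a zero-case rule. But the protocol does not leave the matter open. It states a specific trigger, and an SAP that follows it inherits the weakness.

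A third reply is that the consequences are limited, and much of this stands. The overall primary endpoint is not realistically affected. Section 9.7 calls the study-level final analysis supportive of the global one. A reader might also infer that 0 v 2 would clear the 20% efficacy threshold, but section 9.6 sets that threshold for the primary outcome only. The five-case rule in section 9.5 limits some sparse age comparisons, though not the age-stratified estimates of section 9.2.

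Finally, a reader might want the exact method for all small counts, such as fewer than five cases in an arm. Step 6 does not support that: the two methods broadly agree from one case upward, and at 1 v 10 the exact interval has the higher lower limit.

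**Conclusion.** The concern holds in limited form. As a trigger, non-convergence is unreliable and software-dependent. With zero cases in one arm, widely used routines usually report convergence and an interval of almost no width. With zero vaccine cases that interval is 100% to 100%, where the exact lower limit runs from -432% (0 v 2) through -9% (0 v 5) to 55% (0 v 10).

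The rule is exposed in hospital admission, ICU admission, death, severe disease and sparse age cohorts. The counts are illustrative. The protocol gives no expected numbers for these endpoints, so it does not support saying that zero vaccine cases is likely. The exact limits assume equal person-time; with the simulated unequal follow-up they moved only slightly (for example 54.6% to 55.7% at 0 v 10). The point merits correction, but it does not threaten the primary efficacy conclusion.

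**What to change.** Amend the fallback sentence in section 9.2. The exact conditional (stratified) Poisson method should be used whenever either arm has zero cases in the analysis concerned, or the robust model fails to converge. State that this applies to every efficacy endpoint and every age-stratified analysis, whatever convergence status the software reports. Keep robust Poisson regression otherwise, with no further case-count cut-off.

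The cost is one sentence, since the exact method is already named. The downside is that intervals for zero-case endpoints become much wider: at 0 v 5, for example, the reported lower limit changes from 100% to about -9%. That width reflects the information actually available.

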### **9.3 Safety & Reactogenicity**

Counts and percentages of each local and systemic solicited adverse reaction from diary cards, and all unsolicited AEs and SAEs will be presented for each group.

## 9.4 Immunogenicity

Highly skewed antibody data will be log-transformed prior to analysis. The geometric mean concentration and associated 95% confidence interval will be summarised for each group at each timepoint, by computing the anti-log of the mean difference of the log-transformed data.

The geometric mean concentration at day 28 and the proportion of participants seroconverting to the S-spike protein from day 0 to day 28 will be computed. Comparisons between ChAdOx1 nCoV-19 vaccine and MenACWY groups will be made using a Mann Whitney U test due to the low titres expected in the control group which will cause a non-normal distribution.

In addition, those aged 56 years or older receiving either a single-dose or two-doses of ChAdOx1 nCoV-19 vaccine will be compared with those in phase 1 (COV001) aged 18-55 years who received single-dose ChAdOx1 nCoV-19.

Spike-specific T cell responses (ELISpot) will be presented as means and confidence intervals, or medians and interquartile ranges if non-normally distributed at all post vaccination time points. Comparisons between ChAdOx1 nCoV-19 vaccine and MenACWY groups will be made using a Mann Whitney U test due to the low responses expected in the control group which will cause a non-normal distribution. Comparison between two different dose levels of ChAdOx1 nCoV-19 will be made using t-tests. In addition, those aged 56 years or older receiving either a single-dose or two-doses of ChAdOx1 nCoV-19 vaccine will be compared with those in phase 1 (COV001) aged 18-55 years who received single-dose ChAdOx1 nCoV-19.

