|  | To assess efficacy of the candidate ChAdOx1 nCoV-19 against severe and non-severe COVID-19                                    | 
 
a) Hospital admissions associated with COVID-19
 
b) Intensive care unit (ICU) admissions associated with COVID-19
 
c) Deaths associated with COVID-19
 
d) Seroconversion against non-Spike SARS-CoV-2 antigens
 
e) Severe COVID-19 disease (defined according to clinical severity scales)
 
 | 
Throughout the study
 
See schedule of attendances
 
Throughout the study
 |
|  | To assess humoral immunogenicity of ChAdOx1 nCoV-19                                                                           | 
 
a) Antibodies against SARS-CoV-2 spike protein at Day 28 post-vaccination.
 
b) Proportion of seroconversion to antibodies against SARS-CoV-2 spike protein measured by ELISA at Day 28 post-vaccination.
 
                                                                                                           | Blood samples drawn at Day 0 and Day 28 post-vaccination                                   |
|  | To assess cellular immunity of ChAdOx1 nCoV-19 in older adults (groups 1, 2, 7 and 8 only)                                    | a) Interferon-gamma (IFN- $\gamma$ ) enzyme-linked immunospot (ELISpot) responses to SARS-CoV-2 spike protein;                                                                                                                                                                                                                                                               | See schedule of attendances                                                                |
|  | To assess the safety and immunogenicity of a booster dose of ChAdOx1 nCoV-19 in older adults aged 56 years or older (two-dose | a) occurrence of solicited local reactogenicity signs and symptoms for 7 days following booster vaccination;                                                                                                                                                                                                                                                                 | a) Day 28-35 Self-reported symptoms recorded using electronic diaries                      |

CONFIDENTIAL

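### Section 9.4 defines the geometric mean concentration as the anti-log of a mean difference of logs, which is a ratio of geometric means and not a concentration

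*Protocol*

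**What the plan says.** The passage is section 9.4 Immunogenicity in the Statistics chapter of the protocol (another section 9.4, on adverse events of special interest, sits in the safety chapter). It starts from the log scale: "Highly skewed antibody data will be log-transformed prior to analysis". It then names what will be reported: "The geometric mean concentration and associated 95% confidence interval will be summarised for each group at each timepoint". The same sentence ends with the method: "by computing the anti-log of the mean difference of the log-transformed data". No reference for the difference is given, whether baseline, comparator arm or another visit.

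The next paragraph uses the GMC as a level, to be reported at day 28 beside the share of participants who seroconvert. The comparison with the control arm is separate: "Comparisons between ChAdOx1 nCoV-19 vaccine and MenACWY groups will be made using a Mann Whitney U test".

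Section 4 lists "Antibodies against SARS-CoV-2 spike protein at Day 28 post-vaccination" as a secondary humoral outcome. Spike antibody at day 56 is a secondary outcome for the two-dose schedules in the older groups 1, 2, 7 and 8. Antibody titres recur among the tertiary outcomes, for example one dose against two, persistence, and group 5d against group 11. No other part of the protocol gives a formula for the GMC.

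**The concern.** The quantity and the formula do not match. A GMC is a level in assay units, for one group at one visit. A mean difference of logs needs two sets of values, and its anti-log has no units. Its interval rests on the spread of the differences, or on two groups' variances, and not on the spread of the values at that visit.

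If the sentence were followed, antibody levels would be presented as concentrations when they are ratios. Under a baseline reading, the divisor would be each group's own baseline level, so it need not be the same in groups set side by side. Section 6.3.2 lets seropositive participants into some groups (5d, 5e, 5f, 9, 10 and 11) and not into others, so baseline levels could differ between groups.

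**Working it through.** The protocol attaches no antibody mean, standard deviation or other figure to this point, so there is no stated result to reproduce. The only number is the 95% level. The check is algebra, followed by an illustration with assumed values.

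**Algebra.** Let x be the concentration at the visit and r the reference value.

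- GMC = antilog(mean(log x)), with 95% CI antilog(mean ± t × SD/√n).
- Rule as written: antilog(mean(log x − log r)) = GMC(x) / GMC(r).

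The two point estimates agree only if GMC(r) is exactly 1 unit. If r is the baseline value, then at day 0 every difference is log x − log x = 0. The rule then returns antilog(0) = 1.0 with a zero-width interval in every group, whatever the true level.

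**Illustration (all values assumed).** Take n = 50, a true day-28 GMC of 200, a log10 SD of 0.5 at day 28 and 0.3 at day 0, day-0 and day-28 values uncorrelated, and t = 2.01 on 49 degrees of freedom.

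Correct GMC interval: 2.01 × 0.5/√50 = 0.142 and 10^0.142 = 1.387. The limits are 200/1.387 = 144 and 200 × 1.387 = 277, at any baseline level.

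Rule as written, against baseline: SD of the differences = √(0.5² + 0.3²) = 0.583; 2.01 × 0.583/√50 = 0.166; 10^0.166 = 1.465.

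| Assumed baseline GMC | True day-28 GMC (95% CI) | Rule as written | Interval from the rule |
|---|---|---|---|
| 1 | 200 (144 to 277) | 200/1 = 200 | 137 to 293 |
| 5 | 200 (144 to 277) | 200/5 = 40 | 27 to 59 |
| 20 | 200 (144 to 277) | 200/20 = 10 | 6.8 to 14.6 |

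A constructed sample of 50 with shuffled baseline values gave almost the same intervals: 138 to 290, 28 to 58, and 6.8 to 14.6. Even in the first row, where the point estimate happens to be right, the interval belongs to a different quantity.

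Taking the control arm as the reference gives the same point estimates, 200, 40 and 10, for control GMCs of 1, 5 and 20.

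**The case against.** The strongest reply is that this is a slip of the pen. The sentence names a GMC, per group and visit, on log data. With no reference stated there is nothing to subtract, so the rule cannot be run literally. A statistician would most likely compute the usual GMC, and a column of 1.0 at day 0 would be noticed at once. The protocol also promises a detailed study-level SAP, which is not at hand and may carry the right formula. That is persuasive about what will probably happen, and it keeps the point modest. It does not make the sentence right: this is a stated method that is wrong, not a detail left for later.

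Three stronger readings should be resisted.

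- A reader might infer that the hypothesis tests or the efficacy results are affected. They are not. The vaccine-control comparison is rank-based and does not use the GMC; seroconversion is a proportion; primary efficacy does not rest on antibody levels.
- A reader might infer a fixed size of error, such as ten-fold. The size is simply the reference GMC, which the protocol does not give.
- A reader might extend the criticism to ELISpot, because the section says "Comparison between two different dose levels of ChAdOx1 nCoV-19 will be made using t-tests". The text does not say those tests are on the raw scale, and a choice of transformation is commonly left to the SAP. The reason given for Mann-Whitney is low responses in the control arm, which does not arise between two dose levels of the vaccine. The documents do not support a finding there.

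**Conclusion.** The definition of the GMC in section 9.4 is wrong as written: it describes a ratio of geometric means, with no reference stated, and its interval belongs to that ratio. Against baseline, the reported value would be too small by a factor equal to the baseline GMC when that exceeds 1 unit (1, 5 and 20 in the assumed cases), and 1.0 at day 0 always. The algebra needs no assumptions; the numerical sizes rest wholly on assumed levels and standard deviations.

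The reach is limited to descriptive summaries of secondary and tertiary antibody outcomes. The documents do not show that any reported GMC was or will be wrong, only that following the protocol's sentence would make it so.

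**What to change.** Replace the method clause so that the GMC is *the anti-log of the mean of the log-transformed values, with the 95% CI from the anti-logged confidence limits of that mean*. If a fold rise or a between-group geometric mean ratio is also wanted, add it as a separate quantity: the anti-log of the mean difference of the logs, with the reference (baseline, comparator group or earlier visit) stated. Check that the SAP uses the same definitions.

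The cost is one sentence, or two if a ratio is added. It needs no new data and changes no test, sample size or visit.
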